**Table 6 Tab6:**
[figure not shown]
Schedule of enrolment, interventions, and assessments

*IG* intervention group, *CG* control group

### Study variables

The primary outcome of the study was depressive symptoms and secondary outcomes were 24-h movement behaviors (physical activity, sedentary behavior, and sleep) and basic psychological needs (autonomy, competence, and relatedness). Autonomy, competence, and relatedness variables were also examined as potential mediators influencing the effectiveness of the intervention on depressive symptoms. Furthermore, sociodemographic factors, health conditions, self-perceived health, lifestyle, and factors related to the perception of barriers to practicing physical activity were considered as descriptive and/or adjustment variables.

### Data treatment and statistical analyses

The tabulation of questionnaire data is conducted through the Google Form® platform, which automatically generates an Excel spreadsheet as soon as participants respond to the tools. At the conclusion of the process, the tabulation will be checked manually by the Vincular Project team. Database management and processing, as well as descriptive and inferential analyses, will be performed using different statistical packages, including the Statistical Package for the Social Sciences (SPSS, version 23.0) and RStudio (version 2021.09.0).

Continuous variables will be described using measures of central tendency and variability, while categorical variables will be presented in terms of absolute and relative frequencies, along with their respective 95% confidence intervals. Before applying hypothesis tests, the normality of continuous data will be assessed through (a) kurtosis and asymmetry and (b) the Kolmogorov–Smirnov test. In the absence of normality in the data distribution, non-parametric procedures will be adopted. Comparisons of the measured variables between groups at baseline will be conducted using the Student’s t-test for independent samples (or its non-parametric equivalent, the Mann–Whitney U test), and the Chi-Square test for categorical variables.

To verify the effect of the intervention on the primary outcome and secondary outcomes, per-protocol and intention-to-treat analyses will be conducted. The first one will take into account only IG participants who followed the activities until the last meeting, complied with the planned intervention protocol with at least 50% overall attendance and in each of the four blocks of the intervention, in addition to being duly evaluated in the line moments baseline and post-intervention. This decision aligns with the intervention proposal, in which the initial meetings comprised more theoretical activities, with practical sessions beginning in the second month onwards. Those from the GC who participated in the assessments will also be considered. The second analysis will include all individuals from the CG who participated in both data collections, and those from the IG considered in the per-protocol analyses. To fill in the missing data from the other participants, the multiple imputation technique will be applied, using sex, age, and the variables of interest as predictors. For comparisons between periods (pre- and post-intervention) and between groups (intervention and control), analysis will be conducted using generalized estimating equations (GEE), with Bonferroni post hoc adjustments. The significance threshold will be set at *p* ≤ 0.05. However, for time*group interactions, *p* ≤ 0.10 will be considered marginally significant [126]. Additionally, effect sizes will be calculated based on (a) Cohen’s d [127], considering small values (0.20 ≤ d < 0.50), medium values (0.50 ≤ d < 0.80), and large (d ≥ 0.80); and (b) partial eta squared (ηp2), with small (0.02 ≤ ηp2 < 0.13), medium (0.13 ≤ ηp2 < 0.26), and large (ηp2 ≥ 0.26) effect sizes [128]. These procedures will be performed using the Statistical Package for the Social Sciences (SPSS, version 23.0) software.

To investigate the mediating role of basic psychological needs, structural equation modeling procedures will be adopted, using linear regression models, through the lavaan package in the RStudio software (version 2021.09.0). Diagrams will be created using the “Miro” website (https://miro.com). For the structural equation model, the “SEM” command will be utilized with the MLM estimator: maximum likelihood estimation. In this context, the mediating variable corresponds to an intervening factor essential for completing the causal relationship between an independent variable and a target behavior [129]. In intervention studies, a variable is considered a mediator when it alters the positive relationship between the treatment and the investigative variable (exemplified, in the present study, by the CG and IG and by depressive symptoms, respectively). Different analyses can be employed to identify mediating variables, based on statistical procedures that test the hypothesis that an independent variable (treatment) influences a certain outcome (investigative variable) through one or more mediators [130]. For this type of analysis to occur, a causal chain with at least three variables (independent, mediating, and dependent) is necessary, as illustrated in Fig. 3. In this model, the independent variable (treatment) is represented by “X,” while the mediating variable is “M,” and the dependent/investigative variable, “Y.” Thus, the model assumes a system with different possibilities: (a) the treatment impacting the investigative variable, referred to as the total effect (represented by coefficient “c”); (b) the treatment impacting the mediating variable (coefficient “a”); (c) the mediating variable impacting the dependent/investigative variable, with adjustment for the treatment variable (coefficient “b”); and (d) the treatment impacting the investigative variable, adjusting for the mediating variable, known as direct effect (coefficient “c”). The indirect effect of the treatment on the investigative variable through the mediating variable is calculated as the product of coefficients “a” and “b.” The total effect is calculated by summing the direct and indirect effects (c = c’ + ab) [130].

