Another aspect to be considered concerns the evidence of the effectiveness of fundamental interventions based on Self-Determination Theory across a wide range of health domains [37]. However, there is still a gap in the literature regarding the effectiveness of experimental studies focused on actions aimed at 24-h movement behaviors and supported by Self-Determination Theory in reducing depressive symptoms in adults. As an additional factor, the proposal for an intervention grounded in this theory allows professionals to support basic psychological needs (focused on autonomy, competence, and relatedness), thereby fostering autonomous motivation and behavioral change in participants [36]. This approach is highly particular and little explored in clinical trials, addressing intrapersonal, interpersonal, and environmental themes and their relationship with a healthier lifestyle, thus contributing to the non-pharmacological treatment of depression. Interventions that concentrate on a variety of activities can encourage the exploration of intrinsic feelings. This strategy, based on the principles of Self-Determination Theory, facilitates an increase in individual’s motivation and long-term adherence, making studies more pragmatic, with the results obtained lasting immediately after the conclusion of these programs. This becomes relevant considering that individuals with depressive symptoms experience several barriers, such as lack of energy and loss of interest, common factors associated with the disease itself, and which contribute to the abandonment of health promotion in its most varied contexts.

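### The per-protocol comparison selects the intervention arm on attendance and completion but controls only on being assessed, so it is not randomised, and the plan does not rank it below the ITT analysis

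*Protocol article*

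**What the plan says.** All the rules are in the protocol article, section *Data treatment and statistical analyses*.

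- **Purpose and status.** To verify the effect on primary and secondary outcomes, "per-protocol and intention-to-treat analyses will be conducted". Neither is named primary or supportive.
- **Intervention arm, per-protocol: completion.** "The first one will take into account only IG participants who followed the activities until the last meeting".
- **Intervention arm, per-protocol: attendance.** The same people must have "complied with the planned intervention protocol with at least 50% overall attendance and in each of the four blocks of the intervention". An assessment at both time points is required as well.
- **Control arm, per-protocol.** "Those from the GC who participated in the assessments will also be considered". No adherence condition is set.
- **Analysis called intention-to-treat.** "The second analysis will include all individuals from the CG who participated in both data collections, and those from the IG considered in the per-protocol" set. For everyone else, "the multiple imputation technique will be applied, using sex, age, and the variables of interest as predictors". Attendance is not a named predictor.

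The *Discussion* says that lack of energy and loss of interest are "common factors associated with the disease itself, and which contribute to the abandonment of health promotion".

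**The concern.** Attendance and completion are observed after randomisation and only in the intervention arm. Filtering on them leaves a self-selected part of one arm to be compared with a control arm that was not filtered on adherence. If whatever keeps people attending is related to how their PHQ-9 changes, the groups differ even when the intervention does nothing.

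Two features make this more than the usual caveat on a per-protocol table. The article gives the per-protocol result the same task as the ITT result and does not say which governs if they differ. The ITT analysis also begins from the same filtered intervention set and imputes the rest, so neither analysis clearly uses the observed outcomes of everyone randomised. As written, no clean all-randomised result is there to override a misleading per-protocol one.

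**Working it through.** **Inputs from the article** (*Sample size, randomization, and allocation concealment*): f = 0.25, 80% power, 5% two-tailed, two groups, three time points, N = 28; dropout up to 50%, so 56; allocation 1:1, so 28 per arm.

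**The article's own figure.** Repeated-measures ANOVA, group-by-time interaction, with correlation 0.5 and epsilon 1 assumed because neither is stated: λ = f²·N·m/(1−ρ) = 0.0625 × 28 × 3 / 0.5 = 10.5, with 2 and 52 degrees of freedom. Power is 0.812 at N = 28 and 0.778 at N = 26, so 28 reproduces. Then 28/(1−0.5) = 56.

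**Assumptions for the selection check** (the article gives none of these): no true effect; improvement standardised; correlation r between improvement and the tendency to attend; the top share p of the intervention arm kept; all 28 controls kept. Keeping half (14 of 28) corresponds to the article's upper dropout allowance. Keeping 70% (20 of 28) is a milder case.

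**Formula.** Expected shift in SD of improvement = r × φ(z)/p, where z cuts off the upper share p.

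- p = 0.5: φ(0)/0.5 = 0.399/0.5 = 0.798. For r = 0.1, 0.3, 0.5 the shift is 0.08, 0.24, 0.40.
- p = 0.7: φ(−0.524)/0.7 = 0.348/0.7 = 0.497. The same r give 0.05, 0.15, 0.25.

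**Error rates**, from 20,000 simulated null trials per row with a two-sample t-test, which stands in for the planned GEE:

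| Kept | r | Shift (SD, formula) | p ≤ 0.05, two-sided | False benefit (nominal 2.5%) |
|---|---|---|---|---|
| 14 of 28 | −0.3 | −0.24 | 10.8% | 0.4% |
| 14 of 28 | 0 | 0 | 4.9% | 2.5% |
| 14 of 28 | 0.2 | 0.16 | 7.3% | 6.5% |
| 14 of 28 | 0.3 | 0.24 | 11.1% | 10.7% |
| 14 of 28 | 0.5 | 0.40 | 21.8% | 21.7% |
| 20 of 28 | −0.3 | −0.15 | 7.6% | 0.8% |
| 20 of 28 | 0 | 0 | 4.7% | 2.4% |
| 20 of 28 | 0.2 | 0.10 | 6.0% | 4.7% |
| 20 of 28 | 0.3 | 0.15 | 7.7% | 7.0% |
| 20 of 28 | 0.5 | 0.25 | 12.4% | 12.1% |

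The article also calls time-by-group p ≤ 0.10 marginally significant. At that threshold, 14 kept and r = 0.3 flags 18.6% of null trials, against 9.9% at r = 0.

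**Control losses.** Keeping a random 80% of controls changes little (10.4% two-sided at 14 kept, r = 0.3). If the same selection acted in both arms, the shift is about zero and two-sided error is about 5 to 6%.

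**Selection on baseline severity alone.** Suppose more severe people leave (attendance–severity correlation 0.3, half kept) and attendance has no other link to outcome. The retained intervention group then starts 0.24 SD lower on the baseline score, and its post-intervention score is lower by only ρ × 0.24, where ρ is the baseline–post correlation. Change therefore shifts by (1−ρ) × 0.24 SD against the intervention. At an assumed ρ = 0.5 that is 0.12 SD.

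**The case against.** **The direction is not established.** A reader might infer that the filter must favour the intervention, because the article says symptoms drive abandonment. That statement concerns how symptomatic people are, not how much they improve, while the planned analysis concerns change. Selection on baseline severity alone gives the opposite sign, as shown above. This objection stands: bias towards benefit needs the further assumption that people who are not improving stop attending. That is plausible, but the article does not state it.

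**Controls are not unselected.** They must have been assessed, and *Experimental procedure* expects a high chance of control dropout. This also stands. It removes the bias only if losses in both arms follow the same relation to outcome; random control loss does not.

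**The asymmetry is inherent.** Controls have no sessions to attend, so no attendance rule could apply to them, and the article openly calls the set per-protocol with a threshold fixed in advance. That is fair. It explains why the comparison is not randomised but does not make it so, and it is the reason to give the result a supportive label.

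**Ranking can be left to the analysis plan.** Often true, and silence on ranking alone would be no finding. Here, though, the text assigns both analyses to verify the effect and builds the ITT analysis on the filtered set. That is stated content.

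**A complier-average effect is not a clean replacement.** Correct. Participants below the threshold still receive sessions, the WhatsApp group and take-home tasks, so the assumption that assignment does nothing for them is doubtful.

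**Conclusion.** The point holds in limited form. The per-protocol comparison applies a post-randomisation adherence filter to one arm and an assessment filter only to the other. It is not a randomised comparison and should not carry a claim of effect.

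The possible size is material: roughly 0.05 to 0.40 SD of improvement for assumed correlations of 0.1 to 0.5 with 70% or 50% of the intervention arm kept. At r = 0.3 to 0.5 with half kept, the two-sided error rate is about 11% to 22%. These figures rest on assumed r and p, on all controls being kept, and on a t-test in place of GEE. Keeping 14 of 28 against 28 controls is one scenario, not a forecast.

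The documents do not support saying that the analysis is definitely biased towards benefit, or that the controls are unselected. The bias is zero if attendance is unrelated to improvement and reverses if the relation is negative. The point still matters because the analysis called ITT starts from the same filtered intervention participants and so offers no independent safeguard.

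**What to change.** 1. Name one primary analysis: all randomised participants, compared by assigned arm, using every observed outcome whatever the attendance, with imputation only for outcomes that are truly missing.
2. Label the per-protocol result supportive and non-randomised, and state that no claim of effect rests on it.
3. A complier-average estimate, with randomisation as instrument and the same attendance rule, may be added only as an optional sensitivity analysis. State two limits. Its standard error is about the ITT standard error divided by the compliance share, so it doubles at 50% compliance. It also assumes no effect of attendance below the threshold. If non-compliers gain d_n and compliers gain d_c, the estimate is d_c + d_n × (1−p)/p, with p here the compliance share. At p = 0.5 that is d_c + d_n, so any partial benefit inflates it.

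Items 1 and 2 need only wording, plus the assessments already made of intervention participants who missed the threshold. Item 3 uses attendance data that the 50% rule already requires. Since *Trial status* reports the trial as concluded, the change should be dated and should say whether outcome data had been seen.

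### The analysis labelled intention-to-treat takes its observed intervention-arm data only from per-protocol attenders and imputes everyone else

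*Protocol article*

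**What the plan says.** Under Data treatment and statistical analyses, the Protocol article states that "per-protocol and intention-to-treat analyses will be conducted" for the primary and secondary outcomes.

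The per-protocol set in the intervention group (IG) has three conditions:
- retention: "only IG participants who followed the activities until the last meeting";
- attendance: "with at least 50% overall attendance and in each of the four blocks of the intervention";
- assessment: "in addition to being duly evaluated in the line moments baseline and post-intervention".

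Control group (CG) participants enter if they took part in the assessments.

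The intention-to-treat analysis "will include all individuals from the CG who participated in both data collections, and those from the IG considered in the per-protocol analyses". The next sentence deals with everyone else and names the predictors: "To fill in the missing data from the other participants, the multiple imputation technique will be applied, using sex, age, and the variables of interest". Effects are then estimated by generalized estimating equations on the pre- and post-intervention data. Nowhere does the article say that observed outcomes of low attenders in the intervention group are kept.

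**The concern.** Intention-to-treat means that participants are analysed in the arm to which they were allocated, with their own outcomes, whatever they did afterwards. Here the observed intervention data are chosen by behaviour after randomisation, and the choice is made in one arm only.

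The article itself gives reason to think that attendance is related to outcome. The Introduction and Discussion describe loss of interest and lack of motivation or energy as features of depression that lead people to abandon health programmes, and the sample size section allows for dropout of up to 50%. If attenders differ from low attenders in prognosis or in benefit, imputations learned from attenders do not reproduce what low attenders actually reported.

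At stake is the effect estimate for the primary outcome and the meaning of its label. A reader who sees the two analyses agree would take that as reassurance, although both rest on the same observed intervention data.

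**Working it through.** **Step 1: who is observed and who is imputed.** Attendance and assessment are separate conditions, so four kinds of participant can be set side by side on the natural reading of the text:

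| Participant | Both assessments done | Treated as |
|---|---|---|
| CG, any behaviour | yes | observed |
| IG, meets retention and attendance | yes | observed |
| IG, fails retention or attendance | yes | imputed |
| Either arm | no | imputed |

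The third row is the fault: a score exists but is not used. The filter is also strict. Each block has eight sessions (Experimental procedure), so a person attending 8, 8, 8 and 3 sessions has 27/32 = 84% overall but 3/8 = 37.5% in one block, and falls in the third row even with both assessments complete.

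**Step 2: arm size.** The article gives 28 participants, doubled for 50% dropout: 28/(1 − 0.5) = 56, or 28 per arm at 1:1. This reproduces. The 28 also reproduces (power 0.812) if a correlation of 0.5 between repeated measures and sphericity are assumed; the article states neither. The point here does not depend on the sample size.

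**Step 3: an assumed example.** The article does not give the number or outcomes of assessed low attenders, so these inputs are assumptions. Of 28 in the intervention arm, 14 are attenders with effect −1.0 SD, 8 are assessed low attenders with −0.2 SD, and 6 are lost with 0. Controls are at 0.

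As-randomised effect = (14 × −1.0 + 8 × −0.2 + 6 × 0)/28 = −15.6/28 = −0.557 SD.

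*Imputation within arm.* The other 14 take the attenders' mean, so the estimate is −1.0 SD and the ratio is 1.0/0.557 = 1.8.

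*Imputation pooled over arms,* from the mean of all observed values:

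| Controls observed | Pooled mean | IG mean | CG mean | Difference | Ratio to −0.557 |
|---|---|---|---|---|---|
| 28 | −14/42 = −0.333 | (−14 − 4.667)/28 = −0.667 | 0 | −0.67 | 1.20 |
| 20 | −14/34 = −0.412 | (−14 − 5.765)/28 = −0.706 | 8 × −0.412/28 = −0.118 | −0.59 | 1.06 |
| 14 | −14/28 = −0.500 | (−14 − 7)/28 = −0.750 | 14 × −0.5/28 = −0.250 | −0.50 | 0.90 |

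**Step 4: simulation of the within-arm case.** Assumptions: 28 per arm, 3,000 runs, and low attenders' scores replaced by regression on baseline fitted to the attenders. Values are PHQ-9 points. The comparison analysis uses every outcome.

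| Scenario | Attenders | Planned set | All outcomes used | True as-randomised effect |
|---|---|---|---|---|
| No effect, low attenders 2 points worse by prognosis | 50% | −0.95 | 0.03 | 0 |
| Same | 70% | −0.63 | −0.03 | 0 |
| Effect −3 in attenders only, no prognostic gap | 50% | −2.97 | −1.46 | −1.5 |
| Same | 70% | −3.03 | −2.13 | −2.1 |
| No effect, no gap | 50% | 0.00 | 0.00 | 0 |

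The first two rows are close to the share of low attenders times the gap: 0.5 × 2 = 1.0 and 0.3 × 2 = 0.6. With neither a prognostic gap nor a difference in effect, there is no bias.

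**The case against.** The strongest defence is the phrase about filling in missing data. A PHQ-9 score that was recorded is not missing, so the authors may intend to impute only values never collected. The English is rough in places, and this reading is possible. It is not the natural one, because the sentence just before names the intervention participants who are included, and they are the per-protocol set. If the milder meaning was intended, the text still needs correcting.

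Second, low attenders may mostly have missed the May assessment as well. Few real scores would then be lost, and what remains is the ordinary risk that data are missing for reasons related to outcome, which any trial with heavy dropout shares. This stands as a limit on the size of the problem, not on the fault in the definition.

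Third, an attendance rule in one arm is not wrong for a per-protocol analysis: controls had no sessions to attend, and the article gives a reason for the rule. The objection is only to carrying it into the set labelled intention-to-treat.

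A reader might also infer more than the article supports:
- *That randomisation is broken outright.* Imputation may bring everyone back into the arm allocated, so the head count may be complete. The fault lies in which data count as observed.
- *That the bias must favour the intervention.* This needs imputation within arm and low attenders who do worse. The predictors named are sex, age and the variables of interest; whether allocated arm is among them is not stated.
- *That failing to name a primary analysis set is a further error.* That is commonly left to a statistical analysis plan, which is not shown.

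**Conclusion.** The definition is wrong as written. The set called intention-to-treat restricts observed intervention-arm data by attendance after randomisation, with no matching condition for controls, and nothing else in the article repairs this. Confidence in that is high.

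Confidence in size and direction is low to moderate. The 1.8-fold overstatement holds for the assumed example with within-arm imputation. Pooled imputation in the same example gives 0.9 to 1.2 times the true effect, depending on how many controls are observed. The actual figure depends on three things that the article does not give: how many low attenders were assessed, how they fared, and whether the imputation model contains allocated arm.

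Whatever the size, agreement between the two planned analyses cannot serve as evidence of robustness, because their observed intervention data are the same.

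**What to change.** Redefine the intention-to-treat analysis in the statistical section as follows:
1. Include all randomised participants in the arm to which they were allocated.
2. Use every observed outcome, whatever the attendance or retention in sessions.
3. Impute only assessments that were not obtained, with allocated arm and baseline PHQ-9 in the imputation model.
4. Report the attendance-restricted analysis as supportive, and say that it is not a randomised comparison.

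It would also help to report, by arm, how many participants were assessed post-intervention and how many of those in the intervention arm failed the attendance rule. That shows how much the change matters.

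The trial is concluded and the analyses are still described in the future tense, so the cost is rewording and a little re-analysis of data already collected. The estimate may be less favourable to the intervention. If the authors always meant to keep observed scores from low attenders, only the wording changes.

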### Sample size, randomization, and allocation concealment

The sample size was calculated using G*power 3.1.9.2 software, and was based on an ANOVA model for repeated measures with three time points and two groups. Parameters included an average effect size of 0.25, statistical power of 80%, and 5% significance level for two-tailed tests, reaching a value of 28 individuals. Anticipating a potential dropout rate of up to 50%, the number calculated was doubled, bringing the total sample size to 56 individuals. Eligible individuals were randomly assigned to either the control group (CG), instructed to maintain their usual activities, or the intervention group (IG), which actively participated in the program. To ensure numerical and participant characteristic balance between groups, randomization was stratified by sex, age, and PHQ-9 score, employing a 1:1 ratio. The randomization process was executed using the online platform randomizar.org by researchers not directly involved in the intervention. The allocation list was concealed from all study evaluators.

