### Assessments

The assessment of the variables of interest was carried out at three moments: (a) baseline pre-intervention (January 2023); (b) post-intervention, immediately following the conclusion of the program (May 2023); and (c) post-intervention, 6 months after the end of the intervention (follow-up evaluation, conducted in November 2023). Questionnaires were employed to measure the variables, and participants were required to respond in the presence of a previously trained researcher. To facilitate this process, specific dates and times were scheduled based on participants’ availability. Furthermore, during these assessment periods, participants used accelerometers to objectively measure their 24-h movement behaviors. In Fig. 1, it is possible to observe a schematic diagram with the time schedule of enrolment, interventions, and assessments.

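### The stated imputation model leaves out treatment arm, which shrinks the between-arm effect if data are missing at random within arm; the fix must go together with a corrected intention-to-treat set

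*Protocol article*

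**What the plan says.** The section on data treatment and statistical analyses in the Protocol article sets out two effect analyses, per-protocol and intention-to-treat. Of the second it says: "The second analysis will include all individuals from the CG who participated in both data collections, and those from the IG considered in the per-protocol", meaning the IG members who qualify for the per-protocol analysis. It then turns to everyone else. The purpose of imputation is given as "To fill in the missing data from the other participants", and the method is stated next: "the multiple imputation technique will be applied, using sex, age, and the variables of interest as predictors". For the comparison "between groups (intervention and control), analysis will be conducted using generalized estimating equations (GEE), with Bonferroni post hoc adjustments" are specified, applied to the pre- and post-intervention periods, with a time-by-group interaction.

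Three other places bear on the reading:

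- The Assessments section uses the same phrase for things measured at visits: "The assessment of the variables of interest was carried out at three moments". The Trial status section repeats this use.
- The Study variables section lists outcomes, mediators and descriptive or adjustment variables. It begins "The primary outcome of the study was depressive symptoms and secondary outcomes were 24-h movement behaviors" and does not list allocation.
- The sample size section gives the planning ceiling for loss: "Anticipating a potential dropout rate of up to 50%, the number calculated was doubled, bringing the total sample size to 56 individuals".

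**The concern.** An imputation model should contain every term of the analysis model whose effect is to be estimated. Here the analysis model contains group and group-by-time, and the stated imputation model contains neither. Given the other predictors, such a model fills in missing outcomes as if the arms did not differ.

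The listed predictors cannot make up for this. Randomization was stratified by sex, age and PHQ-9 score, so sex, age and baseline PHQ-9 carry essentially no information on arm. Other post-intervention measures could carry some, but a participant who misses that visit entirely supplies none of them.

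At stake is the intention-to-treat estimate of the primary outcome in a trial that planned for heavy loss.

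**Working it through.** **Planning figures.** The document gives no figure for the imputation itself, so the sample size is checked first, to fix the setting. The stated inputs are: "Parameters included an average effect size of 0.25, statistical power of 80%, and 5% significance level for two-tailed tests, reaching a value of 28 individuals", with three time points and two groups. Assuming a correlation of 0.5 between repeated measures and no sphericity correction (neither is stated), the within-between interaction has noncentrality λ = f²·N·m/(1−ρ) = 0.0625 × 28 × 3 / 0.5 = 10.5 on 2 and 52 degrees of freedom. Power is 0.812. Then 28/(1 − 0.5) = 56. Both stated figures reproduce. At 1:1 allocation this is 28 per arm.

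**Closed form for the shrinkage.** Let Δ be the arm difference, m₁ and m₀ the missing fractions in the intervention group (IG) and control group (CG), and let data be missing at random within arm. On the scale where the control mean is 0, the observed participants have pooled mean wΔ, where w = (1−m₁)/[(1−m₁)+(1−m₀)]. An arm-blind model imputes around wΔ in both arms.

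- Completed IG mean: (1−m₁)Δ + m₁wΔ
- Completed CG mean: m₀wΔ
- Share of Δ retained: (1−m₁) + w(m₁−m₀)

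With m₁ = m₀ = m this is exactly 1−m. With unequal loss, for example 50% in IG and 20% in CG, w = 0.5/1.3 = 0.385 and the share is 0.5 + 0.385 × 0.3 = 0.615.

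**Simulation check.** The settings were 28 per arm, normal-regression multiple imputation with 10 imputations, predictors sex, age and baseline outcome, with or without arm, and Rubin's rules. Data were missing completely at random. The true effect of 1 SD and the baseline–post correlation of 0.5 are assumptions.

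| Missing IG / CG | Closed form, no arm | Simulated, no arm | Simulated, with arm |
|---|---|---|---|
| 10% / 10% | 0.90 | 0.899 | 1.008 |
| 20% / 20% | 0.80 | 0.780 | 0.990 |
| 30% / 30% | 0.70 | 0.727 | 1.013 |
| 50% / 50% | 0.50 | 0.497 | 0.996 |
| 50% / 25% | 0.60 | 0.598 | 0.996 |
| 50% / 0% | 0.667 | 0.659 | 0.994 |

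The small gaps at 20% and 30% come mainly from whole numbers of participants: 6 of 28 missing gives 1 − 6/28 = 0.786, and 8 of 28 gives 0.714. At 50% missing in both arms, illustrative power for the assumed 1 SD effect is about 11% without arm and 66% with arm.

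**If other post-intervention data exist.** Suppose those missing PHQ-9 still supply another post-intervention measure that the intervention shifts by an assumed 0.8 SD. The share retained at 50% missing then rises from 0.50 to 0.67 or 0.74, depending on how closely that measure tracks PHQ-9 (assumed residual correlation of 0.3 or 0.6 in size).

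**Interaction with the analysis set.** Now drop missing-at-random within the IG. Suppose per-protocol attenders gain 1.0 SD, non-attenders gain nothing, half of the IG is not per-protocol, and controls are missing at random. The true intention-to-treat effect is 0.5 × 1.0 + 0.5 × 0 = 0.50 SD. With the IG observed data restricted to attenders:

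- arm-blind imputation with 20% of CG missing gives 0.615 SD, which is too large;
- arm-blind imputation with 50% of CG missing gives 0.50 SD, right by coincidence;
- adding arm, with the set unchanged, gives about 1.0 SD, twice the truth.

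**The case against.** The strongest reply has four parts.

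*The text is condensed and does not expressly exclude arm.* This is true. The phrase for the assessed measures is never formally defined, and imputing within each arm would also be compatible with a list that does not name arm as a predictor. But a predictor list is given, not left for later. The document's own use of the phrase is for things assessed at visits, which allocation is not. An analyst following the text would leave arm out. If arm was intended, one word settles it.

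*The shrinkage figures are conditional.* This also stands. The 50% is a planning ceiling, actual missingness is not reported, and the effect size and correlation in the simulation are assumptions. There is a November assessment, and IG members below the attendance threshold may have been assessed in May, so some imputed participants may have other follow-up data that carry information on arm. The shrinkage is then weaker, though still present.

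*A reader might infer that the intention-to-treat estimate is bound to be biased towards zero.* The document does not support that. The result holds under missing-at-random within arm, but the plan takes IG outcomes only from attenders who met the attendance rule. As the last calculation shows, the arm-blind estimate can lie above, or coincide with, the true intention-to-treat effect.

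*A reader might also infer that adding arm is a complete remedy.* It is not. With the IG set as written, an arm-specific model would impute non-attenders as if they had attended, and could move the estimate further from the target.

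**Conclusion.** The point holds in conditional form. The stated imputation model omits the factor whose effect the GEE then tests. If data are missing at random within arm and the whole post-intervention visit is missed, the between-arm effect is retained at about 80%, 70% and 50% when 20%, 30% and 50% of both arms are missing. With unequal loss, shrinkage somewhat exceeds the overall missing share: 50% in IG and none in CG is 25% overall but loses a third of the effect. Observed follow-up measures on the imputed participants lessen the loss.

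Read literally, the plan also imputes IG members who were assessed but fell short of the attendance rule, so the imputed share can exceed true dropout. The omission of arm and the restriction of IG data to attenders can pull in opposite directions. No net direction against the true intention-to-treat effect can be stated from the document, and an accidental offset between the two is no reason to keep either. The per-protocol analysis is not affected by the imputation model.

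**What to change.** Make two changes together.

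1. Include treatment arm in the imputation model as a main effect, or impute separately by arm if numbers allow. At 50% loss only about 14 observed participants per arm would remain, so the main effect is the safer default.
2. Use the observed outcomes of all randomized participants, whatever their attendance, so that only outcomes that are truly missing are imputed.

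An arm-by-baseline term and antidepressant use at screening are optional refinements. Baseline PHQ-9 is already among the predictors on the document's own use of the phrase, but naming it would remove doubt, as would saying whether the November measures are included. Attendance can be used only within the IG, because controls had no meetings to attend.

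The cost is re-specifying the imputation and the intention-to-treat set. The document still words these analyses in the future tense, and no new data are needed.
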